## Abstract

Individuals with neuromuscular disorders display a combination of motor control deficits and lower limb weakness contributing to knee extension deficiency characterized by exaggerated stance phase knee flexion. There is a lack of evidence for long-term improvement of knee extension deficiency with currently available clinical treatment programs. Our previous work testing a wearable robotic exoskeleton with precisely timed assistive torque applied at the knee showed immediate increases in knee extension during walking for children with cerebral palsy, which continued to improve over an acute practice period. When we applied interleaved assistance and resistance to knee extension, we observed improvements in knee extension and increased muscle activation indicating the potential for muscle strengthening when used over time. There is a need for additional, high-quality trials to assess the impact of dosage, intensity and volume of training necessary to see persistent improvement in lower limb function for these patient populations. This randomized crossover study (ClinicalTrials.gov: NCT05726591) was designed to determine whether 12 weeks of overground gait training with a robotic exoskeleton outside of the clinical setting, following an initial in clinic accommodation period, has a beneficial effect on walking ability, muscle activity and overall motor function. Participants will be randomized to either complete the exoskeleton intervention or continue their standard therapy for 12 weeks first, followed by a crossover to the other study component. The primary outcome measure is change in peak knee extension angle during walking; secondary outcome measures include gait speed, strength, and validated clinical scales of motor function and mobility. Assessments will be completed before and after the intervention and at 6 weeks post-intervention, and safety and compliance will be monitored throughout. We hypothesize that the 12-week exoskeleton intervention outside the clinical setting will show greater improvements in study outcome measures than the standard therapy.

## Introduction

The standard of care for treating knee extension deficiency in neuromuscular disorders includes some combination of three approaches: surgical interventions, chemodenervation procedures (i.e. Botulinum toxin injections), and physical therapy. Controlled studies and interventional trials of available treatments indicate long-term improvement in knee extension deficiency remains variable. Surgical outcomes can be unpredictable and there is evidence for weakening and ambulatory decline in the long term [1, 2]. Botulinum toxin injections may result in a temporary or limited improvement in overactivity or muscle spasticity but do not address the primary problem or ameliorate long-term deficits [3, 4]. Botulinum toxin injections are generally used in tandem with physical therapy to optimize results. Physical therapy programs include strength training, such as progressive resistance training of knee extensors [5], or gait training either overground or treadmill-based. Gait training allows the child to be full weight bearing, to train with body weight support, or to be guided by robotic assistance thereby enabling the rehabilitation program to be tailored to each child’s unique needs. These methods have shown a range of results demonstrating effectiveness for children with cerebral palsy at improving gait speed [6] and mobility, reducing loads on the lower limbs to allow improved upright posture and increasing walking endurance as a result of overall improvement in gross motor function [7–10].

Within the category of device augmented therapies are robotic-assisted gait trainers (RAGT). These devices contrast with body-weight support treadmill training because they strap the user into a multi-joint (hip, knee and ankle) powered robotic system that can assist with walking in all or part of the gait cycle without requiring user or therapist driven assistance [11]. Early versions of RAGT were treadmill-based, which limited their useable environment to the clinical setting and does not accurately replicate the demands on the lower-extremities during overground walking [12]. Additionally, the device and treadmill belt will continue to operate regardless of user effort, so it can be difficult to determine whether a child is actively or passively engaged with the device [12]. A study of ambulatory children with bilateral cerebral palsy found decreased volition in motor control and muscle activation of the legs when walking with a robot-assisted gait trainer on the treadmill [13].

The challenges of treadmill-based RAGT has led to recent proliferation in wearable robotic exoskeleton technology for pediatric populations [14]. Exoskeletons offer modularity in design and implementation; some devices which target more affected individuals span the trunk and the legs, offering support at multiple joints and even can incorporate motorized walkers for support [15, 16]. Exoskeletons which span multiple joints can also adapt the assistance strategy to the individual user, and recent efforts have focused on advanced control approaches to achieve this goal [17–20]. Other devices target single joints such as the ankle [21] or knee [22–24] in ambulatory individuals who walk with a gait pathology such as knee extension deficiency or drop foot. Initial cohort studies of these technologies, performed mostly in clinical settings, demonstrate their effectiveness as assistive devices to improve gait biomechanics including increases in gait speed, step length, ankle plantarflexion, knee extension, hip extension, walking distance and reduction in metabolic energy cost [15, 25–27].

Whereas these results demonstrate that device augmented therapies may assist mobility, their promise as therapeutic technologies to improve long term function is less clear. Initial clinical studies have shown some potential for rehabilitation gains after exoskeleton-mediated gait training. For example, programs that utilize multi-joint exoskeletons to provide assistive forces to aid walking have shown increases in gait speed and step length [13, 15]. A two-phase clinical gait training program utilizing a multi-joint exoskeleton with partial body weight support, wherein the first phase focused on moving the limbs according to a target gait pattern while the second phase encouraged active participation via progressive reduction in assistance, showed improvements in strength and gait performance metrics in four children with CP [28]. An alternative approach is to utilize robotic devices to provide resistance during walking as form of training. A tethered pelvic-based system that applied downward force during treadmill walking resulted in improved step length and knee extension after 15 sessions (3 per week, 5 weeks) of training [29]. Other approaches that have provided targeted resistance to the ankle during treadmill walking using tethered [30] and untethered [31] approaches showed increases in preferred walking speed after the training period, as well as reduction in metabolic cost of transport, improved 6-minute walk test, and increased plantarflexor muscle activation [32]. While these findings demonstrate the potential for exoskeleton facilitated gait training to improve function, they have yet to be evaluated in randomized trials. Further, these studies utilized clinic-based training sessions, which do not fully leverage the wearable technology that can facilitate delivery of gait therapy in a range of settings, thereby increasing the therapy dosage and intensity.

To address these limitations in currently available therapies, we designed a novel wearable robotic exoskeleton for overground use in children with knee extension deficiency. The device applies extensor torque at precisely timed portions of the gait cycle to assist knee extension during walking. In early testing, we found the device encouraged volitional muscle activity assessed by increased surface EMG coincident with improved knee extension [33]. When applied to an observational cohort study of children with crouch gait from cerebral palsy under a previous, IRB approved protocol (#13-CC-0210) at the NIH Clinical Center, the device was found to be safe for overground use and effective at altering posture, gait biomechanics and muscle activity during use in a clinical lab setting [25, 26, 34]. The observed mean improvements in knee extension (13 degrees) were similar to those of invasive surgeries [1]. A range of responses to the exoskeleton were also observed in this initial cohort, motivating the pursuit of more-individual specific control strategies as well as developing hardware that was more powerful and untethered, which would expand its potential environment of use. A case study on a child with CP found that the second-generation NIH pediatric robotic exoskeleton, or P.REX, improved the subject’s walking mechanics during use. This new version of the device deployed an adaptive mechanism characterized by assistive torque applied proportionally to the individual’s estimated knee extension moment in stance phase of the gait cycle. These results suggested the potential to personalize control strategies to each user [23], which would allow the device to be tailored to the unique demands of subjects across neuromuscular disorders. The second-generation P.REX device also incorporated an optional functional electrical stimulation (FES) unit, which can deliver stimulation to the knee extensor muscles that is precisely timed to the gait cycle phase and synchronized with the robotic assistance or resistance [35].

Following these initial findings, a new, novel wearable robotic exoskeleton (NIH-Agilik) was developed with an expanded target population to include children with cerebral palsy, spina bifida, muscular dystrophy or incomplete spinal cord injury [36]. This device had a slimmer profile, was more power efficient, and incorporated a user-friendly interface to control the device settings, offering the potential to be applied outside of the clinical setting after initial safety and feasibility testing. The NIH-Agilik is capable of applying torque bidirectionally (i.e., extensor or flexor) to assist or resist knee movement. Torque profiles, which are defined by specifying the torque magnitude and direction and the ramp on and ramp off rate, can be independently set for five phases of the gait cycle: early, mid- and late stance and early and late swing phase, enabling the overall torque profile during the stride to be tailored to each individual user [36]. This capability broadens the exoskeleton’s use-case by providing a tool to leverage the benefits of strength training with the possibility to improve selective motor control by delivering precisely targeted resistance to challenge functional movement. Thus, whereas an exoskeleton that applies only assistive torques to make walking easier can have broad rehabilitative effects associated with increased walking duration and enhanced neuromuscular and cardiovascular activity, one that applies resistive torques can target specific muscle groups and/or functions for improvement, in this case knee extension during walking. Additionally, by interleaving exoskeleton provided assistive and resistive torques within and/or between strides, it is possible to extend this targeted rehabilitation approach to individuals who may be too weak or have too poor selective motor control to utilize an exoskeleton intervention that only resists movement. Indeed, this interleaved approach may be most suitable for children who have the least functional mobility and consequently are at the highest risk for losing the ability to walk.

We piloted an interleaved strategy with the NIH-Agilik exoskeleton that applied resistance to knee extension during late swing phase, which must be overcome by the user to complete each step, while also applying assistance to knee extension during early and mid-stance phase to provide antigravity support and maintain forward momentum [36]. This approach pursues the complementary goals of knee extensor strengthening to address the lower limb weakness and improved selective motor control by providing on-demand resistance during phases of active knee extension, while also leveraging the assistive torques to increase training duration. The immediate effects of this interleaved assistance and resistance control strategy on the biomechanics and neuromuscular activity of a single subject with cerebral palsy (GMFCS level III) were recently tested to establish initial feasibility of this strategy [36]. The control system displayed a high level of accuracy in providing appropriately timed torque to assist and resist knee extension during overground walking, resulting in immediate improvement in knee extension and simultaneous increase in knee extensor muscle activation, demonstrating the potential for strengthening after prolonged use [36].

Clinical and basic neuroscience suggests high intensity and high dosage training is necessary to achieve functional improvement via motor learning [37, 38] and the exoskeleton intervention being studied in this protocol leverages these key features in multiple ways. The exoskeleton applies resistance to knee extension during walking, which requires an intense and specific motor response to overcome, which itself can strengthen muscles and the synaptic connections required to activate them. Because the exoskeleton is wearable and can be used overground in multiple settings, the error-augmenting flexor torque can be delivered at a high dosage (hundreds or thousands of steps each day). It also elicits a desirable after-effect of increased knee extensor muscle activity, and potentially increased knee extension, that can then be reinforced on a regular and extended basis as the user walks without the exoskeleton between training sessions. Evidence for gait training with wearable robotics in community and home settings is extremely limited. Given the intervention’s combination of multiple motor learning principles, the NIH-Agilik’s safe and effective overground operation, and preliminary findings of an immediate benefit from NIH-Agilik’s use on biomechanics, neuromuscular activity and functional ability, there is strong merit for its investigation outside of the clinical setting. The purpose of this study is to evaluate safety, dosing and initial efficacy of a wearable exoskeleton for overground gait training in home or community environments over a 12-week training period.

## Materials and methods

### Objectives and endpoints

The overall goal of this protocol is to evaluate our intensive 12-week community-based exoskeleton training program. The International Classification of Functioning, Disability, and Health (ICF) provides a comprehensive framework for description and assessment of functional abilities split across four domains: body structures and functions, activities and participation, personal, and environmental factors [39, 40]. The ultimate goal of an intervention study is to improve activity and participation. Given this is analogous to a phase I study, our endpoints here aim to evaluate changes at the ICF level of function and activity, with the goal to provide an initial body of evidence to support more comprehensive studies of this and similar technologies in the future.

The primary objective is to evaluate the safety and effectiveness of a longitudinal community exoskeleton training program to improve crouch gait in children with CP or knee extension deficiency in children with MD, SB, or iSCI. To evaluate this objective, the primary endpoint is change in peak knee angle during midstance phase of walking (without the exoskeleton) between two time points: the initial and final outcome assessments. These assessments occur immediately before and after the 12-week community-based exoskeleton training period. A clinically significant improvement in peak knee extension will be considered here as greater than 10°, based on a study characterizing children with crouch gait as mild, moderate or severe in terms of 10° increments [41]. This change in peak knee extension will also be compared to the change measured between the assessments immediately before and after the 12-week standard therapy period as a secondary endpoint. This outcome is at the ICF level of body structure and function.

The secondary objectives at the ICF level of body structure and function are as follows.

To evaluate peak and overall volitional knee extensor muscle (vastii, rectus femoris) activation during walking. The associated endpoint is change in knee extensor muscle activation between two time points: the initial and final outcome assessments. This outcome will be assessed using surface EMG recorded during walking. Peak muscle activation will be measured as the greatest EMG activity within a stride, and overall knee extensor activation will be measured by area under the normalized EMG curve as in [26].To evaluate change in knee extensor muscle strength following completion of the 12-week community robotic exoskeleton use. Knee extensor strength will be assessed using the Biodex dynamometer while seated with a knee angle of 60 degrees to measure the maximum isometric knee extension torque, between the initial and final outcome assessments.To evaluate persistence of improvement in peak knee extension (primary endpoint) at six weeks post completion of robotic exoskeleton training.

The following secondary endpoints at the ICF level of activity will be evaluated.

The change in average gait speed during overground walking before and after robotic exoskeleton training. Gait speed will be assessed using two endpoints: walking overground using the Vicon Motion Capture system and the 6-minute walk test.The improvement in gross motor function following robotic exoskeleton gait training. This will be measured using three validated functional instruments, the Timed Up-and-Go test [42], the GMFM-66 assessment [43] and the PEDI-CAT [44].

Like the primary endpoint, changes in the secondary endpoints from the exoskeleton intervention period will be compared with changes measured before and after the standard therapy period. We also will evaluate a number of exploratory objectives.

The safety and feasibility of the community-based exoskeleton gait training program assessed by recording adverse events and side effects, which will be split into two categories: (a) minor or anticipated side effects and (b) serious or unanticipated side effects. Feasibility will be assessed as a measure of compliance to study parameters, by determining whether the individual met the suggested dosage of device use while in the community.We will evaluate the primary endpoint (peak knee extension at midstance) as a function of dosage by comparing this parameter across multiple time points: Baseline to Initial Assessment (signals completion of in-lab accommodation/training block), Baseline to Intermediate Assessment (signals 50% completion of community use block), Baseline to Final Assessment (signals completion of community use block), and Baseline to Follow-up Assessment (signals 6-weeks post completion of community use block).We will evaluate changes in lower limb muscle spasticity after robotic exoskeleton gait training using the modified Ashworth scale and the Tardieu scale measured at two time points: the initial and final outcome assessment.

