**Fig 2 pone.0304087.g002:**
[figure not shown]
Schematic diagram of the randomized, cross-over protocol. Yellow indicates the 12-week block for exoskeleton set-up and in-lab accommodation. Pink indicates the 12-week block for community exoskeleton use, including a 6-week follow up period. Blue indicates the 12-week block for standard therapy in the community.

The design is structured as a randomized crossover study with two intervention arms: (i) exoskeleton intervention and (ii) standard therapy control (Fig 2). The crossover design was chosen to maximize participation by allowing all participants to receive the exoskeleton intervention. After enrollment, each participant will be randomized into one of two groups: Group A will receive the exoskeleton intervention first, followed by standard therapy control, while Group B will complete standard therapy control first before crossing over to receive the exoskeleton intervention. Continuation of the participant’s existing standard therapy was chosen as the control due to limited resources to administer a common program and because individuals in the target populations are often enrolled in a physical therapy regimen. All participants will complete an initial visit for exoskeleton fitting, setup, and calibration as well as multiple in-lab accommodation visits prior to starting the community-based exoskeleton intervention. An alternative option, if the participant is not able to complete the community use portion of the protocol for any reason, is to continue the intervention by completing a lab-based exoskeleton training consisting of 10 total visits, each with a target of 1-hour total of walking with the exoskeleton. The target intervention dosage in the community will be held constant across all subjects who participate at 1 hour/day, 5 days/week. Outcomes from individuals who complete the lab-based training will be analyzed separately from those who complete the community-based intervention. The maximum possible number of visits to NIH for completion of this study is 19. All visits will take no more than 4 hours to complete. There will be up to six outcome assessments to evaluate our primary, secondary and exploratory objectives.

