
### Study assessments and outcomes

All participants will complete the same study procedures and assessments (S1 Table), only varying in order of completion by Group (Fig 2). Each assessment visit will include collection of all outcome measures as indicated in Table 1. For Group A, assessments will be performed in the following order: at baseline (upon enrollment), initial outcome assessment (after in lab accommodation), intermediate outcome assessment (6 weeks after start of community exoskeleton intervention), final outcome assessment (12 weeks after start of community exoskeleton intervention), follow up outcome assessment (6 weeks after completing community exoskeleton intervention), and standard outcome assessment (12 weeks after starting standard therapy control). For Group B, assessments will be performed as follows: baseline assessment, standard outcome assessment, initial outcome assessment, intermediate outcome assessment, final outcome assessment, and follow up outcome assessment.

**Table 1 pone.0304087.t001:** Outcome measures by ICF domain and data collection timepoints.

Outcome Measure	ICF Domain^1^	Baseline Assessment	Exoskeleton Intervention Assessments				Standard Outcome Assessment
			Initial	Intermediate	Final	Follow-Up	
Peak knee extension (deg)	Body structure	X	X	X	X	X	X
Knee extension at initial contact (deg)	Body structure	X	X	X	X	X	X
Step length (m)	Function	X	X	X	X	X	X
Gait speed (m/s)	Function	X	X	X	X	X	X
Knee moment in stance phase (Nm)	Function	X	X	X	X	X	X
Peak activation of knee extensor (mV/mV)	Function	X	X	X	X	X	X
Mean knee extensor muscle activation (mV/mV)	Function	X	X	X	X	X	X
Gross motor function classification system (GMFCS, I-V)	Function	X	X	(X)^2^	X	X	X
Pediatric evaluation of disability inventory–computer adaptive test (PEDI-CAT, scaled 20–80)	Activity	X	X	(X)	X	X	X
Gross motor function measure (GMFM-66, scored 0–198)	Activity	X	X	(X)	X	X	X
6-minute walk test (6MWT, m)	Function	X	X	(X)	X	X	X
Timed up and go (s)	Function	X	X	(X)	X	X	X
Knee extensor spasticity (Modified Ashworth scale, 0–4)	Body structure	X	X	(X)	X	X	X
Knee extensor spasticity (Tardieu scale, deg)	Body structure	X	X	(X)	X	X	X
Knee extensor isometric strength (Nm)	Function	X	X	(X)	X	X	X
Knee flexor isometric strength (Nm)	Function	X	X	(X)	X	X	X
Quebec User Evaluation of Satisfaction with Assistive Technology 2.0 (QUEST 2.0)	Activity				X		

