Our continuous data outcomes will be summarized using descriptive statistics and presented as means with standard deviation. We will summarize our categorical data as a range with percentages. The primary endpoint, peak knee angle at midstance, will be analyzed using a per-protocol analysis to include all participants who completed at least 80% (9 weeks) of the study intervention in the community using a paired t-test between the initial and final outcome assessments. Similarly, a paired t-test will be utilized to compare change in the primary endpoint of peak knee extension with the change observed over the 12-week standard therapy block. Given the potential for carryover effects, this secondary outcome will only be assessed using data from the first intervention period from each group. We will test for normality and if not found, we will use the signed rank test instead of the paired t-test. Given the potential heterogeneity within each participant pool, we anticipate the possibility for a wide range of responses in the endpoints following the intervention. To address this potential variability, we will also perform a post-hoc linear regression analysis to assess potential effects of age, weight/height, and mobility (characterized by functional scale GMFCS I-IV) on each endpoint. We will perform an interim analysis of the primary endpoint when we have reached 50% of the estimated recruitment number to evaluate the effect and the power and revise the total enrollment number if indicated.

The same statistical procedures will be used for the secondary outcome measures and exploratory outcome measures that evaluate continuous data between multiple time points. We will report the 95% confidence intervals, in addition to the mean difference and statistical significance of that difference, for each endpoint. For the exploratory analysis of dosage effect across all four outcome assessments, we will use a repeated measures ANOVA.

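### The exploratory dosage contrasts start from Baseline in both groups, but Group B's Baseline comes before 12 weeks of standard therapy without the exoskeleton

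*Protocol article*

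**What the plan says.** Under Objectives and endpoints, an exploratory objective reads: "We will evaluate the primary endpoint (peak knee extension at midstance) as a function of dosage by comparing this parameter across multiple time points". It then lists four contrasts, all starting at Baseline. The first is "Baseline to Initial Assessment (signals completion of in-lab accommodation/training block"; the next two are "Baseline to Intermediate Assessment (signals 50% completion of community use block), Baseline to Final Assessment (signals completion of community use block"; the fourth runs from Baseline to Follow-up, six weeks after community use ends. Each contrast is tied to an exoskeleton milestone, and none is defined differently by group.

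Study assessments and outcomes gives the visit order. Group A is assessed "at baseline (upon enrollment), initial outcome assessment (after in lab accommodation", and its standard-therapy visit comes last. The order then changes: "For Group B, assessments will be performed as follows: baseline assessment, standard outcome assessment, initial outcome assessment". The intervening visit is the "standard outcome assessment (12 weeks after starting standard therapy control". The design text after Fig 2 agrees: "Group B will complete standard therapy control first before crossing over to receive the exoskeleton intervention".

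Statistical considerations names the method: "For the exploratory analysis of dosage effect across all four outcome assessments, we will use a repeated measures ANOVA". It states no sequence term and no group-specific reference visit.

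**The concern.** A contrast offered as the effect of exoskeleton dose should begin when exposure begins, or at a comparable point just before it, in every participant. Here that is true of Group A only. In Group B the same contrast also includes a full block of standard therapy, and whatever change occurs in that block is counted as change with dose.

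Such change is plausible. The Discussion says that these children grow and develop naturally and regularly receive therapy meant to maintain or improve function. Study population says that the gait pathology tends to worsen with age, so the drift could go either way.

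At stake are the reported Baseline-referenced changes for an objective that bears on dosing, which the Introduction names among the study's purposes. Two groups with the same exoskeleton exposure would be averaged over different elapsed times.

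**Working it through.** The documents give no figure for this analysis, so there is none to reproduce. The check builds the timeline and follows the extra block through the pooled contrast.

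**Inputs**
- Set-up and in-lab accommodation block: 12 weeks (Fig 2 caption).
- Standard-therapy block: 12 weeks (Study assessments and outcomes).
- Intermediate and Final: 6 and 12 weeks after community use starts. Follow-up: 6 weeks after it ends (same section).
- Group B's share of participants, w: not stated. 1:1 is assumed (w = 1/2), with 1/3 and 2/3 as a range.
- Mean change in peak knee extension over 12 weeks of standard therapy, c: not given. -3 to +3 degrees is assumed for illustration.

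**Step 1: nominal weeks from Baseline**, taking the blocks as consecutive. Group A: Initial 12; Intermediate 12 + 6 = 18; Final 12 + 12 = 24; Follow-up 24 + 6 = 30. Group B adds 12 to each.

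| Contrast from Baseline to | Group A (weeks) | Group B (weeks) | Standard-therapy block as share of Group B interval |
|---|---|---|---|
| Initial | 12 | 24 | 12/24 = 50% |
| Intermediate | 18 | 30 | 12/30 = 40% |
| Final | 24 | 36 | 12/36 = 33% |
| Follow-up | 30 | 42 | 12/42 = 29% |

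In Group A the standard-therapy block makes up 0% of every interval.

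**Step 2: shift in the pooled contrast.** Let a_k be the mean change to visit k measured from the last pre-exoskeleton visit, taken as equal in the two groups. Group A's Baseline contrast is a_k and Group B's is a_k + c. The pooled contrast is

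(1 - w) a_k + w (a_k + c) = a_k + w c.

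- w = 1/2: 0.5 × (±3) = ±1.5 degrees.
- w = 1/3: ±1.0 degrees.
- w = 2/3: ±2.0 degrees.

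**Step 3: what cancels.** For two later visits j and k, (a_k + w c) - (a_j + w c) = a_k - a_j. The shift drops out of every difference among Initial, Intermediate, Final and Follow-up.

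**Step 4: the ANOVA.** The same algebra was checked on one simulated data set (13 participants, a 3-degree shift in 6 of them). With only the four later visits as levels, F was 4.585 with and without the shift. With Baseline added as a fifth level, F went from 9.47 without the shift to 14.66 with it. These values only illustrate the mechanism; they do not predict the trial's result.

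**Step 5: after changing the reference.** Measured from the Standard Outcome Assessment, Group B's nominal intervals become 12, 18, 24 and 30 weeks, the same as Group A's, and the w c term disappears.

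**The case against.** The strongest reply is that the damage is narrow. The extra 12 weeks come before any exoskeleton exposure, so they add one constant to all four Group B contrasts. Table 1 places exactly four visits under the exoskeleton intervention, and the four assessments in the ANOVA sentence can naturally be read as those. On that reading the planned test of the time effect is untouched. This stands. A reader might infer that the whole dose-response analysis is confounded, but Steps 3 and 4 do not support that. The levels of the Baseline-referenced changes remain affected, and the objective defines its contrasts as exactly those changes.

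A reader might also infer three further faults that the documents do not bear out.
- *A miscount of visits.* Five time points appear in the objective and four in the ANOVA sentence, but four contrasts and four exoskeleton visits fit the text. At most, it is left open whether Baseline is an ANOVA level.
- *Follow-up mistaken for added dose.* The contrast is openly labelled as post-training, and persistence at six weeks is already a separate secondary objective.
- *A bias that flatters the exoskeleton.* The sign of c is unknown. Nor is the 10-degree threshold a suitable yardstick, because it is defined for the Initial-to-Final change.

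Could another provision already cure the problem? The restriction to first-period data applies only to the comparison between interventions. The growth covariate in the Discussion is conditional and concerns differences between the two treatment periods. Adherence as a possible correlate does not alter the reference visit.

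Finally, this detail cannot simply be left to an analysis plan that is not shown, because the article itself fixes Baseline as the reference.

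**Conclusion.** The concern holds in limited form. As written, every Baseline-referenced dosage contrast in Group B includes 12 weeks of standard therapy without the exoskeleton, and none in Group A does. Pooled contrasts shift by w c: -1.5 to +1.5 degrees for an assumed c of -3 to +3 and assumed 1:1 allocation, and up to 2.0 degrees either way if two thirds of participants are in Group B. The shift weighs most, proportionally, on Baseline to Initial, where standard therapy is half of Group B's interval. It also enters any ANOVA that has Baseline as a level.

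It does not affect differences among the four later visits, the primary Initial-to-Final endpoint, or the first-period comparison with standard therapy. The objective is exploratory, so the consequence is modest.

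The week counts are nominal sums from the text and the Fig 2 caption, since the figures are not shown. The defect itself needs only the stated visit order.

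**What to change.** For the dosage contrasts, and for any ANOVA that includes the reference visit, define the reference as the last assessment before exoskeleton set-up: Baseline in Group A and the Standard Outcome Assessment in Group B. State whether that reference visit is a level of the ANOVA.

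Table 1 already schedules peak knee extension at the Standard Outcome Assessment, so the change needs no new visit or measurement, only a sentence in the protocol or analysis plan. Using Initial as the reference in both groups would also remove the shift, but would lose the accommodation step that the first contrast is meant to describe. A model on logged hours of use could be added by preference, but is not needed to correct this point.
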